### Effectiveness Objectives

The primary effectiveness objective of this study is to compare the effectiveness of the Essential Coaching for Every Mother program to standard care on self-efficacy measured immediately after the intervention. The secondary objectives are (1) to compare the effectiveness of the Essential Coaching for Every Mother program to standard care on social support, postpartum anxiety, and postpartum depression immediately after the intervention; (2) to determine whether the effect on any outcomes differs based on parity (multiparous or primiparous); and (3) to compare any long-term impacts of the Essential Coaching for Every Mother program on the above outcomes at 6 months postpartum.

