### Screening and Baseline

Interested participants will contact the research team via text message to complete the automatic remote eligibility screening process. All participants will receive a welcome message as well as details about the study and what the study will entail. During the antenatal recruitment process, the woman’s phone number, first name, and due date will be collected via TextIt [30]. This information is required to ensure that follow-up messages are sent to the woman via her mobile device based on her due date.

During the antenatal screening process, participants will be screened for eligibility, and eligible participants will be informed of the need to send a text within 10 days after giving birth to be enrolled in the study. Women who have not yet given birth are sent messages at 39 weeks, 40 weeks, 41 weeks, and 42 weeks or until enrolled or withdrawn to remind them of the need to text the word “delivered” after giving birth. Participants who initiate contact before 37 weeks will be asked if they want to be sent follow-up messages once they reach 37 weeks until the sample size is reached.

Once a woman gives birth or enrolls after giving birth, she will be asked screening questions to ensure eligibility and determine parity for stratification. Additional details including the newborn’s name, preferred gender pronoun for the infant, infant’s date of birth, and parity will be collected at that time. Once stratified, participants will be randomized and informed of their group allocation. Participants who are randomized to the intervention group will be asked their preference on breastfeeding and formula feeding messages. All participants will be asked to complete the consent form and baseline survey. To remind participants to complete the survey, reminder text messages will be sent via TextIt every other day for 2 weeks (a maximum of 6 total messages) or until the survey is completed. An email will be sent as a final reminder to participants who have not yet completed the survey after day 14. If an email address was not provided, an expanded text message will be sent on day 14 instead. Participants will also be informed that they may message “STOP” to withdraw from the study at any time. If a participant withdraws from the study, they will not receive any further messages nor will they be asked to complete any future surveys. Participants who complete the baseline survey will receive an electronic gift card worth Can $15 (US $11.97).

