### Follow-Up Assessments

At both 6 weeks and 6 months postpartum, all participants in both groups will be sent a text message asking them to complete a follow-up survey. Participants will be asked to provide consent, and once consent is given, they will start the survey. Participants who complete the follow-up surveys will receive an electronic gift card worth Can $15 (US $11.97) for each survey. To remind participants to complete the survey, reminder text messages will be sent via TextIt every other day for 2 weeks (a maximum of 6 total messages) or until the survey is completed. An email will be sent as a final reminder to participants who have not yet completed the survey after day 14. If an email address was not provided, an expanded text message will be sent on day 14 instead.

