### Sample Size

The sample size was calculated based on the primary outcome of self-efficacy using the findings from our feasibility study [24], which showed a mean difference in self-efficacy scores between baseline and 6-week follow-up of 3.78 (SD 4.5). Therefore, with stratification by parity and a moderate intraclass correlation of ρ=0.2, a sample size of 30 participants per cluster and 60 participants per group (120 total participants) is required to be powered for analysis at the level of parity. In the feasibility study, there was an incompletion rate of 15.5%; thus, the estimated sample size will be increased by 15% to 69 participants per group, rounded up to 70 participants. In total, 140 participants will be enrolled in the study.

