### Program Content and Design

#### Text Messages

Essential Coaching for Every Mother consists of 53 standardized text messages that provide evidence-based information related to caring for a newborn and maternal mental health that all new mothers should know. Messages will be sent to participants from birth to 6 weeks postpartum, with 2 messages per day in the first 2 weeks and a daily message in weeks 3 through 6. The following topics are covered in the messages: postpartum anxiety, postpartum depression, maternal self-care, postnatal follow-up, breastfeeding or formula feeding, feeding, infant concerns, cord care, well-baby care, normal development, crying, and safe sleep. Women who receive the messages will be able to self-select breastfeeding or formula feeding messages. The TextIt platform will be used to program and schedule the messages [30], and Twilio will be used as the gateway service that offers virtual phone numbers and short codes that send and receive messages on behalf of the TextIt account [31].

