#### Control Group

Participants in the control group will receive the standard in-person care in the hospital in which they give birth. Women in the control group will not receive any study text messages but are not limited in their ability to seek additional postpartum support outside of the study. Data will be collected for both groups regarding postpartum support sought.

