### Data Analysis

Data will be analyzed on an intention-to-treat basis (excluding women who requested to stop receiving the messages or were lost to follow-up). Demographic characteristics on maternal age, marital status, education level, and delivery method will be expressed as means and standard deviations or percentages, as applicable, based on group allocation. Postnatal contacts for themselves and their infants, health concerns, and feeding behavior will also be expressed as means and standard deviations or percentages, as applicable, based on group allocation. Any significant differences in baseline characteristics, examined through a chi-square analysis or Mann-Whitney test, will be adjusted for in the analysis. A *P* value of 0.05 will be considered significant for all outcomes.

For the primary outcome of self-efficacy, a total score will be reported using means, standard deviations, and percentages. Analysis of covariance (ANCOVA) will be used to measure whether total self-efficacy scores differ between the 2 groups, with adjustments for the pretest scores and any significant baseline characteristics.

For the first secondary objective, an ANCOVA will be used to determine whether scores differ between the 2 groups on social support, postpartum anxiety, and postpartum depression, with adjustments for the pretest scores and any significant baseline characteristics. For the second secondary objective, a 2-way ANCOVA will be used to measure whether the mean difference of self-efficacy scores differs between the 4 groups (multiparous/primiparous and intervention/control), with adjustments for any significant covariates on self-efficacy, social support, postpartum anxiety, and postpartum depression. For the third secondary objective, a 2-way repeated-measures ANCOVA will be used to explore whether changes in the key psychosocial outcome variables varied over time.

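### The only exit described, STOP, ends survey requests along with the messages, so primary-outcome loss can differ by arm; no way to stop the texts and stay in follow-up is described

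*Protocol article*

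**What the plan says.** The Screening and Baseline section sets the rule: "Participants will also be informed that they may message “STOP” to withdraw from the study at any time". It then gives the consequence: "If a participant withdraws from the study, they will not receive any further messages nor will they be asked to complete any future surveys". No other exit is described anywhere in the article.

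The trigger is not shared equally. The Text Messages section schedules 53 messages for the intervention arm, "with 2 messages per day in the first 2 weeks and a daily message in weeks 3 through 6". For the other arm, the Control Group section says: "Women in the control group will not receive any study text messages". Both arms do get survey contacts. Under Follow-Up Assessments, at 6 weeks and 6 months "all participants in both groups will be sent a text message asking them to complete a follow-up survey", with up to six text reminders per survey and a final email, or a longer text where no email address was given.

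The primary objective concerns the effect "on self-efficacy measured immediately after the intervention", that is, the 6-week survey. The Data Analysis section calls the analysis intention-to-treat but qualifies it as "excluding women who requested to stop receiving the messages or were lost to follow-up".

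**The concern.** Stopping the programme and leaving the study are different acts. The first is a response to the intervention; the second withdraws permission to be followed. Here one reply does both. A woman tired of two texts a day, but willing to fill in a questionnaire, has no described route to say so.

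Two things follow. First, dissatisfaction with programme texts can arise in one arm only, so this cause of missing primary data is tied to allocation. Controls can also text STOP, but only in reaction to survey contacts. Second, the outcome is never requested, so no later choice of analysis set recovers it. A missing-data model can only replace it with assumptions.

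The implementation objective is touched as well. Programme feedback, including what women disliked, is gathered in the 6-week survey (Implementation Outcomes). Women who leave because of the texts are never sent it. The withdrawal count, itself an implementation measure, cannot separate rejecting the texts from leaving the study.

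**Working it through.** **The plan's own allowance.** Sample Size takes 60 per group and adds 15%: 60 × 1.15 = 69, rounded to 70. This reproduces. The feasibility incompletion rate was 15.5%, and one rate is applied to both arms, so no arm-specific loss is planned for. At 15.5% loss, 70 × 0.845 = 59.15 women per arm give a 6-week score.

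**Inputs for the illustration**
- SD 4.5 and planning difference 3.78: Sample Size. The SD is reported with the baseline-to-6-week difference, so using it as the spread of 6-week scores is an assumption.
- q, the extra share of otherwise-observed intervention women lost through STOP: not in the documents; assumed 5% and 10%, with no matching loss in controls.
- g, how far below the remaining women they would have scored: not in the documents; assumed 2 and 4.5 points.

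**Shift in the completer contrast.** If those who stay average m, the full-arm mean is (1 − q)m + q(m − g) = m − qg. The completer mean is therefore too high by q × g.
- Low: 0.05 × 2 = 0.10 points, or 0.10 / 3.78 = 2.6% of the planning difference.
- High: 0.10 × 4.5 = 0.45 points, or 0.45 / 3.78 = 11.9%.

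If those who stop would have scored higher than those who stay, g is negative and the shift has the opposite sign.

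**Effect on the test when there is no true effect.** Standard error = 4.5 × √(1/59.15 + 1/n), with n the remaining intervention women; two-sided 5% level assumed, no gain from baseline adjustment.
- Low: n = 59.15 × 0.95 = 56.2; SE = 0.838; shift/SE = 0.119; error = Φ(−1.841) + Φ(−2.079) = 5.2%.
- High: n = 59.15 × 0.90 = 53.2; SE = 0.850; shift/SE = 0.529; error = Φ(−1.431) + Φ(−2.489) = 8.3%.

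**Effect on power.** With n = 53.2 and a true difference of 3.78, power = Φ(3.78/0.850 − 1.96) = Φ(2.487) = 0.994, against 0.995 with no extra loss. Lost numbers are not the issue at the planning effect; selective loss is.

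**The case against.** The strongest reply is that the rule is consistent with itself. Women are told that STOP means leaving the study, and ending all contact afterwards honours that. The article condenses a fuller protocol, and a partial opt-out may exist there or in the TextIt flow. The Data Analysis section names asking for the messages to stop as a category of its own, which could point to a separate route or could be loose wording for STOP. This lowers certainty about practice. It does not remove the point, because the article does not leave the matter open: it states one exit and its consequence.

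Four stronger readings are tempting and are not supported.
- **That every woman who wants fewer texts loses her primary outcome.** Nothing says she would use STOP, and only a STOP sent before the 6-week survey is completed loses that score. A later one costs 6-month data only.
- **That 15.5% measures STOP use.** It is total incompletion in the feasibility study, all causes together.
- **That the bias favours the programme.** Overwhelmed women might stop, but so might confident or experienced mothers who find basic advice redundant. No section supports either direction.
- **That the Follow-Up Assessments section contradicts the withdrawal rule.** Its reference to all participants is ordinary wording; a withdrawn woman need not count as one.

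It is also fair that women unwilling to receive texts are excluded at entry, that both arms are told about STOP, and that the ANCOVA adjusts for pretest score. Any deficit already visible at baseline would be partly removed, so the shifts above are before that reduction.

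**Conclusion.** The point holds as a design weakness. As described, the plan ties the end of the intervention to the end of outcome collection, and the texts most likely to prompt that step go to one arm. Following the plan as written can therefore lose 6-week primary outcomes in a way that depends on allocation and may be informative.

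Its size and direction are unknown. Under the stated assumptions the shift is 0.1 to 0.45 KPCS points, with two-sided error of 5.2% to 8.3% under no true effect. Those figures rest on assumed stopping rates, assumed deficits, no matching control loss and an SD borrowed from the feasibility change score. They show what is possible, not what is expected. The case for acting is that outcomes not requested cannot be recovered, while the change is small.

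**What to change.** 1. Add a message-only opt-out to the TextIt flow, for example a different reply word, and tell participants about it. Keep STOP as full study withdrawal.
2. Amend Screening and Baseline so that women who stop only the messages are still sent the 6-week and 6-month surveys.
3. Record message-stop and study withdrawal as separate dated events, reported by arm.
4. Amend Data Analysis at the same time, so that women who stop the messages but provide outcomes are analysed in the group to which they were randomised. Without this, the data gained under steps 1 and 2 would be discarded.

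Cost: an ethics amendment while recruitment is under way. The new option should apply to participants who have been informed of it, and the meaning of STOP should not change for women already enrolled. There would be some extra survey texts and gift cards. If 10% of the 70 intervention women used the option and completed both later surveys, that is 7 × 2 × Can $15 = Can $210. No additional participants are needed.

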### Randomization

Using a 1:1 allocation, participants will be randomized into either the intervention group or the control group using the “split randomly” function within the TextIt platform [30]. This function randomly passes contacts through approximately equally distributed pathways in the flow and will allocate them to receive either the intervention or the control condition. Randomization will occur after a participant has given birth. Participants will be stratified into 2 groups based on parity (primiparous and multiparous) prior to randomization.

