## Methods

### Study Design

This study will be a 2-group, stratified, parallel-arm, hybrid type 1 effectiveness-implementation randomized controlled trial. Through the use of an effectiveness-implementation design, it is possible to evaluate intervention effectiveness while simultaneously evaluating real-world implementation to guide future development and revisions [25]. The intervention will be compared with standard care that is currently being provided across Nova Scotia, stratified by parity.

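### As described, allocation within parity strata is unrestricted, so stratification does not balance parity between arms, and equal arms and 30 women per parity-by-arm cell are not assured

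*Protocol article*

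**What the plan says.** Study Design calls the trial a "2-group, stratified, parallel-arm, hybrid type 1 effectiveness-implementation randomized controlled trial". Under Randomization, the ratio is stated as "Using a 1:1 allocation, participants will be randomized into either the intervention group or the control group", by means of a random-split function in the TextIt messaging platform. The function's behaviour is described: "This function randomly passes contacts through approximately equally distributed pathways in the flow". On strata, the section says "Participants will be stratified into 2 groups based on parity (primiparous and multiparous) prior to randomization". The Blinding section confirms that randomisation takes place directly in the platform.

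The Sample Size section relies on the four cells formed by parity and arm: "a sample size of 30 participants per cluster and 60 participants per group (120 total participants) is required", and this number "is required to be powered for analysis at the level of parity". It inflates 60 per group by 15% to 69, rounds to 70 and enrols 140. It reports 15.5% incompletion in the feasibility study.

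Under Data Analysis, the primary ANCOVA adjusts for the pretest score and for baseline characteristics that differ significantly between arms. Parity enters as a factor only in the two-way ANCOVA for the second secondary objective.

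**The concern.** Stratified randomisation produces balance only when assignment inside each stratum is restricted, for example by permuted blocks. If each woman is assigned independently with probability one half, doing so separately in each stratum changes nothing: the joint distribution of the four cell counts is the same as with no strata.

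The article does more than leave out detail. It names the tool and says how it behaves, and pathways that are only approximately equal suggest independent routing rather than a scheme that holds the counts together.

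Two things are at stake. The label of a stratified design promises balance on parity that the described method does not give. And the sample size counts on 30 women in each of four cells, which the method leaves to chance. Parity is the one factor chosen for stratification and the subject of a named secondary objective, yet the primary ANCOVA is not certain to adjust for it.

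**Working it through.** **Inputs from the protocol article.** Sample Size: difference 3.78, SD 4.5; 30 per cell, 60 per group, 120 in total; 15% inflation to 140; incompletion 15.5%. Randomization: 1:1. Data Analysis: significance level 0.05.

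**Assumptions, not in the article.** Two-sided test; 90% power; independent 50:50 assignment; 70 primiparous and 70 multiparous women unless another mix is given; losses independent at 15.5%.

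**1. The plan's own figure.** Per arm within one parity stratum, n = 2 × (1.960 + 1.282)² × 4.5² / 3.78² = 29.8, so 30. Four cells give 120. Then 60 × 1.15 = 69, rounded to 70 per group, 140 in total. The stated figure is reproduced at 90% power (80% would give 23 per cell).

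**2. Arm sizes, X ~ Binomial(140, 0.5).**
- SD = √(140 × 0.25) = 5.9; 95% range 58 to 82.
- P(exactly 70:70) = 0.067.
- P(one arm below 60) = 2 × P(X ≤ 59) = 0.076.
- P(arms differ by 20 or more) = 2 × P(X ≤ 60) = 0.108.

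**3. Cell sizes at randomisation, X ~ Binomial(70, 0.5) in each stratum.**
- 95% range 27 to 43.
- P(the two cells differ by 10 or more) = 2 × P(X ≤ 30) = 0.28.
- P(one cell below 30) = 2 × P(X ≤ 29) = 0.188.
- P(at least one of the four cells below 30) = 1 − (1 − 0.188)² = 0.34, so all four reach 30 in about 66% of trials.

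Blocking within parity would give 35 per cell and make that last figure 100%.

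**4. Parity balance between arms.** The difference between arms in the proportion primiparous has an SD of about √(0.25 × (1/70 + 1/70)) = 0.085. Summing over the exact binomial distributions with 70 women per stratum, it exceeds 10 percentage points in 27% of trials. The figure is identical without stratification. Blocking would bring it close to zero.

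**5. Completers per cell at 15.5% incompletion.** A cell of 35 keeps 35 × 0.845 = 29.6 on average.
- Blocked, 35 per cell: P(Binomial(35, 0.845) ≥ 30) = 0.536, and 0.536⁴ = 0.08 for all four cells.
- Unrestricted: 0.015 for all four cells.

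Median size of the smallest completing cell, from 400,000 simulated trials:

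| Parity mix (assumed) | Unrestricted | Blocked |
|---|---|---|
| 50:50 | 25 | 27 |
| 60:40 | 21 | 23 |
| 65:35 | 18 | 20 |

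Blocking recovers about two women in each row. The rest of the shortfall comes from the parity mix and from losses.

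**6. Power cost of imbalance.** Power = Φ(3.78 / (4.5 × √(1/n₁ + 1/n₂)) − 1.960).
- Within a stratum: 35:35 gives 0.940; 27:43 gives 0.928.
- Overall: 70:70 gives 0.999; 58:82 gives 0.998.

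**The case against.** **It is a reading of the text.** The section never says that each assignment is independent, and the platform's documentation is not at hand. A full protocol might describe a restriction. This stands as a caution: unrestricted assignment is a strong inference, not a stated fact. It does not remove the point, because the article describes the mechanism and no restriction appears in it.

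**A reader might infer that 1:1 allocation and 30 per cell are not delivered.** The documents do not support that. An equal-probability split is 1:1 in expectation, and with 70 women per stratum all four cells reach 30 at randomisation about two times in three. They are simply not assured.

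**A reader might also infer that parity confounds the comparison.** It does not in the sense of bias. Imbalance under unrestricted randomisation is chance imbalance, the treatment comparison remains valid, and the power loss is slight. The article also gives partial protection: parity is a factor in the two-way ANCOVA, and a significant baseline difference triggers adjustment. But that trigger is a significance test, so moderate imbalance in parity can go unadjusted in the primary analysis.

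**Most of the cell shortfall has other causes.** This stands. The parity mix and the losses account for most of it, and blocking with 70 women per stratum would still leave 30 completers in all four cells in only about 8% of trials. A condensed article may also leave a parity quota to the full protocol, so its absence is not raised as a separate fault.

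**Conclusion.** The point holds in limited form. On the natural reading of the Randomization section, stratifying by parity has no balancing effect, and equal arms and 30 women per cell are left to chance. With 70 women per stratum (assumed), at least one cell starts below 30 in about 34% of trials, and the arms differ by more than 10 points in the proportion primiparous in about 27%.

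The consequence is moderate. The primary comparison stays valid and keeps almost all its power, and a 27:43 split within a stratum costs about one percentage point of power on the plan's own inputs. What fails is the match between the stratified label, the cell figure in the sample size and the allocation method described. It should be corrected, but it does not threaten the trial's main result.

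**What to change.** Preferred: replace the platform's random split with a pre-generated permuted-block list for each parity stratum, read automatically by the enrolment flow, and describe it in the Randomization section.

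If recruitment is too far advanced, or the platform cannot read such a list, state that allocation is unrestricted. Then include parity as a covariate in the primary and secondary ANCOVAs in every case, not only when a baseline test is significant.

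In either case, reword the Sample Size section so that 30 per parity-by-arm cell is a target that is not guaranteed, and say that parity mix and incompletion also reduce the cells.

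Cost: the blocked list needs set-up and testing in the flow. Because recruitment began in January 2021, it would also be a mid-trial change of allocation method, to be documented with its date. The covariate route costs a sentence in Data Analysis and one degree of freedom.
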